While we believe that the present study will not pose unacceptable risks to volunteers, we will not be overly reassuring to potential volunteers.  With all subjects, whatever their level of drug use, we talk about the pharmacology of MDA-like drugs, risks, reasons for stopping use, and treatment alternatives and referrals.  Among other risks, our consent form (and discussions with potential volunteers) will indicate the possibility of neurotoxicity and its largely unknown consequences.  We believe we can do this in a clear manner that even the most concerned neurotoxicity researcher should consider more than adequate.  It is very important to us that our research not be misconstrued as indicating that illicit MDA use is safe or that MDA or MDMA has any benefits. Recent reviews by members of our group have emphasized the importance of demand reduction in responding to the MDMA epidemic [125] and the very real risks of possible neurotoxicity [126]. As we see it, cautious clinical research is necessary precisely because MDA has high abuse potential and considerable (though poorly understood) potential for toxicity.

Risks of MDA and MDMA Addiction:  There are no reports of MDA addiction.  However, because of their pharmacological similarities, MDA may contribute to MDMA addiction in users of both drugs.  A significant but poorly quantified proportion of MDMA users develop MDMA-related abuse and dependence disorders.  We will administer MDA to on-going MDMA users; therefore, it is important to consider whether these exposures will increase volunteer's risk of MDA abuse or dependence.  There are a number of reasons why drug use is not likely to be increased by study participation.  The dose we will administer is modest compared to abused doses.  Also, this study requires volunteers to abstain from drug use while in it, which can only have a salutary effect on frequency of drug use.  Studies administering addictive drugs of abuse to ongoing users have not found that study participation increases use of drugs [127-129].  It has also been our experience, in conducting many studies like the present one, where participation typically makes individuals more thoughtful and conscious of their drug use and its consequences.  Nonetheless, we will discuss risks of abuse and dependence and its accompanying life impairments with all volunteers.  Discussion includes reasons for quitting and treatment referrals.

Limitations on Nicotine (Tobacco) and Caffeine Use: One important aspect of being in a hospital is that smoking is not allowed.  Smokers may feel irritable or anxious and it is likely that they will feel the desire to smoke.  We will ask that subjects use less than two cups of coffee (200 mg caffeine) on the day before and morning of the experimental session.  If subjects typically drink larger amounts of caffeinated drinks, he/she may feel irritable, tired, and may develop a headache. If they feel that it would be overly difficult for them to limit nicotine or caffeine intake, then they will be requested not to participate in this study.

Catheterization:  Study involves the insertion of a catheter into a forearm vein for blood sampling.  The longest the catheter is kept in place is 10 hours.  This has been well tolerated by subjects in previous studies.  Aseptic technique is always used in inserting the catheters and the risk of infection is small.  In order to reduce the discomfort of needle insertion, an ointment containing a local anesthetic (lidocaine) will be made available and applied to participants' arms if they choose.
  
Blood Loss: Total amount of blood withdrawal during the second screen visit and the post-study follow up will be approximately 51 ml. Blood withdrawal during the two challenge sessions will be approximately 146 ml per session. The total blood loss during this study period of about 4 weeks will be 343 ml. Slow removal of this amount of blood pose little risk to healthy subjects.

No subjects will be restricted from receiving standard therapies during the study.  We screen out subjects receiving therapies that do not fit our inclusion/exclusion criteria.  If therapies become medically necessary for a subject, that subject will be temporarily suspended or permanently discontinued from the study, as appropriate.

Risk of Loss of Confidentiality.  Confidentiality and Privacy.  There is a potential for loss of privacy for participants in this experiment.  The results of test scores, details of past drug history, past medical history, etc., will be kept confidential.  The investigators will do the best they can in keeping locked files and using code numbers wherever possible.  

Nonetheless, it will be common knowledge that participants in this experiment are required to have past use of MDA or MDMA.  Therefore, in the consent form and in discussions, we caution potential participants that anyone having strong concerns about their past use of drug use being revealed should not participate in this research.  To minimize these risks, we are applying for a Certificate of Confidentiality.  

PROTECTION AGAINST RISK

Volunteer Discontinuation, Dropout or Dismissal.  A volunteer may drop out of the study at any time if he/she so chooses or if the investigator feels it is clinically appropriate.  A volunteer will be dismissed from the study due to a serious or unexpected adverse experience or a serious concurrent illness that warrants withdrawal of the subject from the study.  Subjects who use illicit drugs that could interact with study drugs or who otherwise fail to follow study procedures can be dismissed.  

Subject Safety Monitoring and Test Termination.  Using self-report questionnaires and a general medical exam with a physician, nurse, or nurse practitioner, subjects will be screened to eliminate those with significant medical or psychiatric problems.  Special attention is given to allergies and past adverse reactions to MDA, MDMA, and any other stimulants or hallucinogens. If adverse effects should occur, medical treatment will be immediately available. We have extensive experience in measurements in pharmacology/pharmacodynamic studies. A hospital maintained crash cart, oxygen and emergency ventilation equipment (Ambubags) are immediately available. Physiological monitoring of blood pressure, heart rate, body temperature, and subjective ratings will be carried out before dosing and until acute effects resolve (typically around 6 hrs) to ensure that there are no serious adverse physical or psychological effects of MDA.  Throughout the study, particular attention is paid to the rare MDMA-related acute hyperthermia that might also occur with MDA.  Methods of protecting against this risk are described below. 
Hyperthermia:  We monitor core and skin temperature.  Core temperature is measured with a swallowed disposable transmitter (mini-Mitter or similar).  If the disposable transmitter is not functioning properly, tympanic temperature will be recorded using infrared tympanic device.  The two temperatures (and ambient temperature) are displayed continuously during the session for safety monitoring.  Skin temperature is monitored with a thermocouple touching an appropriate surface.  For scientific purposes, temperature is recorded at scheduled intervals after MDA, as described above.
Risk factors for hyperthermia are believed to include high drug dose, dehydration, exercise, and high ambient temperature.  For example, Henry and Rella (2001) write that “it seems apparent that cases of severe hyperthermia and deaths from heatstroke [after MDMA use] were due mainly to prolonged dancing without rest and without drinking enough liquid to allow for normal temperature control through sweating.”  All these risk factors will be absent in our clinical setting.

Definition of dose-limiting toxicity:  Vital signs will be frequently monitored with blood pressure and temperature.  If we exceed stopping criteria in more than one subject we will stop all dosing pending review by all regulatory parties.  The stopping criteria are:
1.	HR > 160, or < 40 or the degree of change is more than 40% from baseline.
2.	SBP > 180, or < 80 or the degree of change is more than 40% from baseline.
3.	DBP > 105, or < 50 or the degree of change is more than 40% from baseline.
4.	Respiratory rate > 28 or < 8, core temperature change > 1 degree C.

In addition, the study will be stopped if any of these serious adverse events occur:
1.	[Na+] ± 6 mEq/L in 12 h
2.	[Na+] ± 6 mEq/L between sessions
3.	Confusion, agitation, delirium, uncontrolled anxiety or aggression.
4.	Muscle weakness, convulsion, or any type of involuntary motor dysfunction.
5.	Reported palpitations, chest pain or chest oppression, flushing, or fainting.
6.	Uncontrollable headache, discomfort, nausea, or vomiting.
7.	Any other serious adverse effect regarded as being due to MDA.

Safety (Go/No Go) Criteria: We have developed conservative criteria to determine the safety of allowing participation in the study and, once accepted, for administering MDA.  Criteria are assessed on admission and prior to dosing with MDA  

The criteria for administering MDA are:

1.	Satisfy inclusion/exclusion criteria (listed above)
2.	Urine toxicology reveals no recent use of MDA or other related drugs 
3.	Have vital signs with heart rates <100 and >50 and systolic blood pressure <135 and >95 and diastolic blood pressure <85 and >50 and respiratory rate <20 and >10; tympanic temperature of 37±0.5˚C and arterial O2 saturation <92%. 

Any severe adverse events will be promptly reported to all relevant regulatory (IRB, FDA, CRAP, CHR) and funding (NIDA) agencies.

Treatment and Compensation for Injury. This will be according to standard CPMC policy.  

(5c) Alternatives: 

This is research, not treatment.  The alternative is to not participate.

6.	QUALIFICATIONS OF INVESTIGATORS: 

[name] has experience administering closely related drugs (MDMA and methamphetamine) to human subjects in protocols similar to the one presented here.  [name] has expertise in pharmacology and has conducted research with MDMA users that did not involve drug administration.  [name] has conducted research similar to this one with [name] for many years.  

7.	BIBLIOGRAPHY: 

1.	de la Torre, R., et al., Pharmacology of MDMA in humans. Ann N Y Acad Sci, 2000. 914: p. 225-37.
2.	Camilleri, A.M. and D. Caldicott, Underground pill testing, down under. Forensic Sci Int, 2005. 151(1): p. 53-8.
3.	Roberts, A.F. and F. Alexander, Report on Clinical Evaluation of SKF#5 (Amphidoxamine). 1957, maps.org online bibliography.
4.	Naranjo, C., A.T. Shulgin, and T. Sargent, Evaluation of 3,4-methylenedioxyamphetamine (MDA) as an adjunct to psychotherapy. Med Pharmacol Exp Int J Exp Med, 1967. 17(4): p. 359-64.
5.	Turek, I., R. Soskin, and A.A. Kurland, Methylendedioxyamphetamine (MDA) subjective effects. J Psychedelic Drugs, 1974. 6(1): p. 7-13.
6.	Yensen, R., et al., MDA-assisted psychotherapy with neurotic outpatients: a pilot study. J Nerv Ment Dis, 1976. 163(4): p. 233-45.
7.	Zinberg, N., Observations on the phenomenology of conscious change. Journal of Psychoactive Drugs, 1976. 8(1): p. 59-76.
8.	Naranjo, C., The healing journey: new approaches to consciousness. 1973, New York: Pantheon Books.
9.	Jackson, B. and A. Reed, Jr., Another abusable amphetamine. Jama, 1970. 211(5): p. 830.
10.	Shulgin, A.T., Psychotomimetic drugs: Structure–activity relationships, in Handbook of Psychopharmacology, Vol. 11, L.L. Iversen, S.D. Iversen, and S. Snyder, Editors. 1978, Plenum Press: New York. p. 243-333.

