CLINICAL PHARMACOLOGY OF MDA
3,4-METHYLENEDIOXYAMPHETAMINE

1.	STUDY AIM/PURPOSE: 

This study uses a double-blind, placebo-controlled, to evaluate the effects of MDA (3,4-methylenedioxyamphetamine), an analog and metabolite of MDMA (3,4-methylenedioxymethamphetamine, 'ecstasy').  This drug has been extensively studied for many years, including clinical trials in the 1950s and 1970s.  It has been used nonmedically by people since at least the 1960s and is currently sometimes sold as MDMA.  It appears to have very similar effects to MDMA, but with slightly more LSD-like components.  However, its pharmacokinetics have not been characterized.  Because pharmacokinetics are important for forensic and scientific understanding of this drug, we are conducting this study.  Because it is an MDMA metabolite, its kinetics will clarify the metabolism of MDMA.  In addition, formal measurement of its pharmacodynamics will allow us to compare it to results from our MDMA studies, which will clarify the structure-activity relationships of psychoactive phenethylamines.

Our primary aim is to study the pharmacological effects of MDA in healthy humans.  

Specific Aims
1. To investigate the pharmacokinetics of MDA after a single oral dose.
2. To investigate the pharmacodynamics of MDA after a single oral dose.

Hypotheses
1. MDA will be metabolized to hydroxymethoxyamphetamine (HMA) and dihydroxy-amphetamine (DHA).
2. MDA will produce dose-dependent increases in:
a.	Cardiovascular measures (heart rate, blood pressure, and myocardial oxygen consumption will increase without changing inotropism)
b.	Self-report stimulant-like measures (AVI positive affect)
c.	Self-report entactogen-like measures (IASR affiliativeness)
d.	Self-report hallucinogen-like measures (SDEQ LSD and Ambivalence scales, APZ-OAV visionary restructuralization scale)
e.	Neuroendocrine measures (cortisol, prolactin, and oxytocin)
f.	Social perception and behavior (emotional face task, brief fear of negative evaluation, dot probe task) 

2.	BACKGROUND: 

MDA is an analog and metabolite of MDMA:  As illustrated in Figure 1, MDA differs from MDMA ('ecstasy') by a single N-methyl group.  MDA is also a minor metabolite of MDMA (e.g., [1]).  Studying MDA therefore has potential for elucidating the metabolism and mechanisms of MDMA.  In addition, MDA is a drug of abuse in its own right.  

Figure 1:  Comparison of MDA and MDMA Structures	
		
MDA	MDMA	

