·	Genotyping for COMT, HTTPLR, 5HT2A, and CYP2D6 

Urine testing will include:
·	Urine toxicology screen (opiates, amphetamine, cocaine, benzodiazepines, MDMA) 
·	Urine pregnancy test for female subjects

Determining CYP2D6 status:  CYP2D6 activity is genetically determined and up to 10% of the Caucasian population has deficient CYP2D6 activity [51].  Either genotyping or phenotyping participants can assess CYP2D6 activity.  Biological samples from subjects will be collected once they are admitted to the GCRC and will be tested for CYP2D6.  
A physician, nurse, or nurse practitioner will conduct a physical examination. 
If necessary, such as in cases where screening results are inconclusive and further tests are needed, additional screening visit(s) may be added.
Experimental sessions:
Experimental sessions at the CCRC at San Francisco General Hospital (SFGH).  Two experimental sessions occur over 2 consecutive days.  Prior to admission and immediately preceding experimental sessions 1 and 2, subjects will be administered a urine toxicology screen and—if female—a pregnancy test.  Timed measurements are made before and after drug administration as described below.  Subjects receive one of two dosing conditions (listed below) per session.  
Subjects are monitored closely before and after, until drug effects resolve or post 8 hours (whichever is later).  
Experimental Drug Doses and Conditions: 
Experimental Dosing Conditions are:
1.	MDA placebo
2.	MDA 98 mg/70 kg body weight
      
Dosing Description and Procedures: In accordance with hospital and other regulations, appropriately licensed personnel will be responsible for administering the study drug.  
Experimental dosing occurs with a 2-hour fast before and a 1.5-hour fast after.  Lactose in a gelatin capsule is used for the MDA placebo.  Placebos are identical in appearance to active drugs.  

Rationale for Experimental Dosing Conditions:  Based on clinical studies, the single MDA dose being given in the present study should produce at most moderate intoxication and stimulant effects that should resolve within 8 hours.  Similar MDA doses have been used in other studies.  The dose is slightly lower than used in our MDMA studies to account for the lower molecular weight of MDA vs. MDMA and facilitate comparisons.

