Famous Face task serves as a control task for the Emotional Face Task to ensure that any changes in recognition of emotional expressions are not due to more global changes in face processing. In the task, faces are briefly presented and participants are must indicate which famous face they saw (e.g., Oprah Winfrey, Angelina Jolie, Madonna). The Famous Face task is identical in structure and timing to a single block of the Emotional Face Task and will be given at the same time as that task. The task takes about 4 minutes.  Participants can take a break between trials at any point during the task. 

Visual functioning battery is a brief computerized battery to measure visual abilities.  In separate blocks, participants indicate the direction of motion of objects, the tilt of bars, and the location or identity of shapes or line drawings of objects embedded in different levels of noise.  Participants can take breaks and rest between trials as desired.
Dot probe task is a widely-used computerized measure of the attention-grabbing effects of facial expressions.  In this task, participants press a key to indicate whether pairs of dots are oriented either vertically or horizontally.  This is designed to be very easy.  Before each pair of dots, images of faces are shown and the alteration in response time caused by the face image measures the attentional effects of the face.  The task takes approximately 8 minutes and participants may take a break at any point in the task. 

EEG is recorded from 64 electrodes placed on the surface of the scalp with sampling at 1024 Hz.  Electrodes are snapped into a cap that resembles a swim cap, with six to eight additional electrodes placed on the face to measure eye movements and facial muscles.  Data are collected while eyes are open and closed.  This is done in a subset of participants in order to collect pilot data and assess the viability of making a measure that requires participants remain motionless after receiving a drug that may have stimulant properties.

		(4c) Methods of Data Analysis:  

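### Hypothesis 2 claims dose dependence with only one active dose, and unchanged inotropism with only a test for a difference; neither claim can be supported as written

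*Protocol*

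**What the plan says.** Section 1 (Hypotheses) opens Hypothesis 2 with "MDA will produce dose-dependent increases in" and applies this to all of 2a to 2f: cardiovascular, stimulant-like, entactogen-like, hallucinogen-like, neuroendocrine and social measures. Hypothesis 2a carries a further prediction: "heart rate, blood pressure, and myocardial oxygen consumption will increase without changing inotropism".

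The same section gives Specific Aim 2 as "To investigate the pharmacodynamics of MDA after a single oral dose". Section 4b (Experimental sessions) says "Subjects receive one of two dosing conditions (listed below) per session". The list that follows has placebo and "MDA 98 mg/70 kg body weight", and the dosing rationale refers to "the single MDA dose being given in the present study".

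Section 4c analyses the hypothesis measures by repeated measures ANOVA. Fisher's LSD comparisons follow a significant F test, and the significance level is 0.05. The sample size is justified by the power to detect a difference on one visual analog item. Section 4c also plans a population PK/PD model on data pooled with the group's other MDA studies. Section 4b lists impedance cardiography among the timed measures but names no index of inotropism.

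**The concern.** Two statements in the hypotheses go beyond what the design and the stated analysis can deliver.

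- **Dose dependence.** With one active dose, the only randomised contrast is drug versus placebo. A significant contrast fits a graded response, a threshold or a plateau equally well. An analysis plan cannot repair this, because no analysis creates a second dose level.
- **Unchanged inotropism.** This is a claim of no effect, but the stated rule is a test for a difference. A non-significant F test would not show that the effect is absent.

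At stake is the wording of the conclusions. A report that follows the hypotheses literally could claim a dose-response the trial did not study, or a cardiovascular mechanism that rests on a small, non-significant comparison.

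**Working it through.** **Dose dependence.** No arithmetic applies. Hypothesis 2 needs responses at two or more non-zero doses. The aim, the list of conditions and the dosing rationale each give one. Weight scaling sets the same dose per kilogram for everyone (98/70 = 1.4 mg/kg), so it adds no second level. The estimable contrast is MDA minus placebo.

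**The plan's own sample size.** Section 4c gives 11 subjects for a change of 28±19 points, with 80% power and two-sided 0.05, raised to 12. Exact paired t calculations give:

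- 6 subjects if 19 is the SD of the within-subject difference (28/19 = 1.47 SD);
- 10 subjects if 19 is the SD in each condition with zero correlation (28/(19 × √2) = 1.04 SD).

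The stated 11 is close to the second reading. Either way it is a calculation for detecting a difference and does not bear on a claim of no change.

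**What a non-significant result would mean at N = 12.** Inputs: n = 12 and two-sided 0.05, from section 4c. Assumption: a single paired comparison, with true change d in units of the SD of the within-subject difference. Power = P(|T| > 2.201), where T is noncentral t with 11 degrees of freedom and noncentrality d × √12.

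| True change d | d × √12 | Power | Missed |
|---|---|---|---|
| 0.25 | 0.87 | 12% | 88% |
| 0.5 | 1.73 | 35% | 65% |
| 0.62 | 2.15 | 50% | 50% |
| 0.8 | 2.77 | 71% | 29% |
| 0.89 | 3.08 | 80% | 20% |

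**Precision.** The 95% half-width is 2.201/√12 = 0.64 SD and the 90% half-width is 1.796/√12 = 0.52 SD, each at an observed SD equal to the true one. An estimate of exactly zero would still leave changes of up to about 0.6 SD inside the 95% interval.

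**Chance of a positive no-change finding.** The true difference is set to zero, and success means the whole interval lies within ± margin. That is the probability that |mean difference| + t × s/√12 is below the margin, averaged over the chi-square distribution of s² with 11 degrees of freedom. The protocol gives no margin, so a range is assumed.

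| Margin (SD) | 90% interval (two one-sided tests at 0.05) | 95% interval |
|---|---|---|
| 0.5 | 11% | 3% |
| 0.75 | 57% | 35% |
| 0.9 | 80% | 62% |
| 1.0 | 89% | 77% |

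For 80% power at a margin of 0.5 SD, about 36 subjects are needed with the 90% interval and about 44 with the 95% interval.

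**The case against.** **It is loose wording.** Section 4b calls placebo and MDA dosing conditions, and section 4c calls the two-level factor dose. Both aims say a single dose and no analysis compares active doses. This stands as a description: correcting the phrase changes no data, sample size or planned test. It does not rescue the hypothesis, which as written asserts more than a placebo contrast.

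**The PK/PD model could address exposure-response.** It could describe one. But section 4c assigns the hypothesis measures to the ANOVA, the doses of the other pooled studies are not given, and a concentration-response fit is not a randomised comparison of doses.

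**An index, a margin and an interval criterion belong in an analysis plan.** Largely fair, and their absence alone is not the point. The point is that the protocol fixes a no-change prediction and a difference test that do not match. It is also fair that the protocol nowhere says a P value above 0.05 will be read as no change. A reader might infer that a real inotropic effect would probably be declared absent. That is not supported: even if non-significance were read that way, a miss is more likely than not only below about 0.62 SD.

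**The power figures are simplified.** Impedance cardiography has 11 post-dose times, and the repeated measures model may perform differently from one paired t-test. Section 4c also calls dose a between-subject factor in one place. The pairing used here follows from each subject having both conditions. The figures are illustrative.

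**The Famous Face task.** A reader might extend the point to this task, which "serves as a control task for the Emotional Face Task to ensure that any changes in recognition of emotional expressions are not due to" a wider change in face processing. The documents do not support that. It is a control measure outside Hypothesis 2 with no stated decision rule, and how it is analysed can be left to the analysis plan.

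**Conclusion.** The point holds for two phrases in Hypothesis 2. The dose-dependence claim cannot be supported by the planned comparison for any of 2a to 2f, because there is one active dose; this needs no assumption. The claim of unchanged inotropism cannot be supported by a non-significant difference test in 12 people. A true change of 0.5 SD would be missed about 65% of the time and one of 0.8 SD about 29%, and the 95% half-width is about 0.64 SD. Those figures assume a single paired comparison, and the effect sizes are assumed values in SDs of the within-subject difference.

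A reader might go further and infer that Aim 2 cannot be met whatever the data show. The documents do not support this. Aim 2 is to investigate pharmacodynamics after a single dose, and the placebo contrast serves it. Increases over placebo remain testable. The correction should be made, but it concerns what may be concluded, not whether the trial is worth running.

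**What to change.** 1. In Hypothesis 2, replace the dose-dependence phrase with increases relative to placebo. State that any exposure-response result from the pooled PK/PD model is exploratory. No change to dosing is needed or proposed.
2. For inotropism, name one impedance-cardiography index and report MDA minus placebo with a 95% confidence interval. Conclude no change only if the interval lies within a margin fixed before unblinding; otherwise report the result as inconclusive.
3. State which interval decides. Two one-sided tests at 0.05 correspond to the 90% interval; requiring the 95% interval to fit is stricter.

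The cost is a change of wording, one prespecified index and margin, and one analysis of data already being collected. Choosing a defensible margin takes clinical judgement, since the protocol offers none. The downside is that the no-change statement will often be inconclusive at N = 12: at an assumed margin of 0.5 SD the chance of establishing it is about 11% with the 90% interval and about 3% with the 95% interval, even if the true change is zero.
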